## Assignment of interventions: blinding

### Who will be blinded {17a}

The type of intervention does not allow blinding for either participants or field researchers who will provide advice on the type of regimen. The statistical analysis however will be conducted by a blinded statistician, to minimize potential bias in the data analysis.

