**Methods:**

Forty-eight participants will be assigned to either TRE or control groups using simple randomization. The TRE group will consume their meals during a 10-h period and experience 14 h of fasting. They will also be advised to consume their last meal no later than 20:00. Both groups will receive standard dietary advice. The participants will be followed for 6 weeks. The primary outcome will be changes in PWV. Laboratory measurements, including lipid profile, liver enzyme tests, fasting blood glucose (FBG), insulin concentrations, and insulin resistance, as well as anthropometric data, blood pressure, basal metabolic rate, appetite status, physical activity level, sleep quality, cognitive function, quality of life, and calorie intake, will be evaluated throughout the study.

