## Trial design {8}

This study is designed as a randomized controlled trial (RCT), with parallel groups and an allocation ratio of 1:1, in a superiority design framework. Regarding the allocation of each participant to the control and intervention groups, randomization will be run using computerized random number generation and sealed envelopes will be used to conceal the random allocation. The potential participants will be identified among the population of the PERSIAN Cohort Study in Mashhad University of Medical Sciences and will be recruited through phone calls. Screening, including both physical and laboratory examinations, will be carried out to assess the presence of MetS based on IDF criteria [16]. The study design and planned assessments for each stage of the study are explained in detail, in the following sections, and briefly summarized in Table 1. The study protocol adheres to the checklist of the Standard Protocol Items: Recommendations for Interventional Trials (SPIRIT) guidance (Table 1).

**Table 1 Tab1:** The timeline for the enrollment, intervention, and assessment schedule

	**Timepoint**	**Timeline**				
		**Enrollment**	**Allocation**	**Study period**		
				**Day 1**	**Week 3**	**Week 6**
	**Enrollment**	✔				
	**Eligibility screening**	✔				
	**Informed consent**		✔			
	**Allocation**		✔			

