### Provisions for post-trial care {30}

A general practitioner and a nurse will be present at each visit to monitor the participants’ well-being during and at the end of the session. Following blood sampling, the participants will be assessed for any potential adverse incidents. Signs and symptoms, such as dizziness, puncture site bleeding, shortness of breath, blood pressure, and imbalance, will be carefully evaluated for any necessary intervention.

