### Procedure for unblinding if needed {17b}

Considering that only the statistician will be blinded, unblinding would not be needed in any circumstances.

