#### Arterial compliance (at baseline, weeks 3 and 6)

The participants’ height will first be measured. The measurement will be taken in the morning following at least 6 h of fasting and abstinence from tobacco, alcohol, and caffeine consumption. The measurement will be taken in the supine position with their hands next to the body, following a 5-min rest at room temperature in a silent place [22].

The pulse wave analysis (PWA) will first be recorded, using a Sphygmocor (SphygmoCor Cardiovascular Management System software version 1.3; AtCor Medical Pty. Ltd., Sydney Australia) to assess the participant’s brachial systolic pressure, diastolic pressure, and pulse pressure. Three measurements will be taken and the average will be reported. Following this, aortic parameters including aortic systolic pressure, aortic diastolic pressure, aortic pulse pressure, mean arterial pressure (MAP), and heart rate (HR) will also be reported. Aortic augmented pressure, augmentation index (AIx), and AIx normalized for a heart rate of 75 beats/minute (AIx 75) will be calculated [22].

To measure pulse wave velocity (PWV), a femoral cuff will be fastened around the thigh, as high as possible. Three distances will be determined including the length from the femoral pulse sensation site to the top edge of the femoral cuff, the interval between the sternal notch to the femoral cuff, and the distance from the carotid pulse to the sternal notch in millimeters using a tape measure. The carotid pulse will be palpated and the tonometer will be positioned on it. When a regular carotid pulse is detected, the femoral cuff will be inflated. The detection of carotid waveforms will be continued until green waveforms are yielded. Then, the femoral cuff will deflate and the results will be recorded. The report will include heart rate, pulse wave velocity, and pulse transit time. Pulse transit time is the time taken for the pulse to travel from the carotid artery to the femoral artery, in milliseconds. PWV will be calculated by dividing the distance between the two arteries by the pulse transit time [22].

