### Data management {19}

In the current study, the database will be generated by entering data in the SPSS software version 20. To increase the accuracy of data collection, all data will be collected by the primary investigator. To ensure that the information collected during the study is kept securely and confidentially, each participant will be assigned a code that will be used to identify him throughout the study. Two separate, password-protected databases will be created, one containing the participants’ personal information (to which only the primary investigator will have access) and one containing the coded study data (to which the study team will have access). The written information, e.g., consent forms and any other data input forms will be kept in a locked cupboard in the primary investigator’s office. The final dataset will comprise all data collected on each participant identified using their unique code. Data sharing between investigators through networks will also be password-protected and access will be allowed only by investigators with a link sent by the primary investigator. All passwords will be changed every 3 months for security reasons.

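### PWV, the partly operator-dependent primary outcome, is collected by an unblinded investigator for a reason that does not cover the measuring role, and Table 1 schedules allocation before baseline PWV

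*Protocol article*

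**What the plan says.** The abstract of the protocol article names the primary outcome: "The primary outcome will be changes in PWV". Under Arterial compliance, several steps are done by hand: "The carotid pulse will be palpated and the tonometer will be positioned on it", and three lengths are taken, among them "the distance from the carotid pulse to the sternal notch in millimeters using a tape measure". PWV is the path length divided by the transit time that the device reports.

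On blinding, section {17a} says: "The type of intervention does not allow blinding for either participants or field researchers who will provide advice on the type of regimen". It adds that the statistician will be blinded. Section {17b} then settles the rest: "only the statistician will be blinded". Data management {19} says that "all data will be collected by the primary investigator", and gives accuracy of collection as the purpose.

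Table 1 ("The timeline for the enrollment, intervention, and assessment schedule") ticks allocation in a column of its own, ahead of the study period. The first PWV is ticked under Day 1, and the others under weeks 3 and 6. The Control group section calls day 1 the baseline visit and places a 45-minute nutrition consultation at each of these three visits. Under Expected outcomes, the investigators state that they expect arterial compliance to improve with TRE. The post-trial care section adds that "A general practitioner and a nurse will be present at each visit".

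**The concern.** Participants and dietary advisers cannot be blinded to an eating window. The person who tapes the distances and places the tonometer can be, and the article gives no reason why that person should know the arm. Section {17b} states a decision to leave outcome assessment unblinded, so this is not a detail left to a fuller document.

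The expected direction of benefit is written down, and part of the measurement is in the operator's hands. Any small shift that differs between arms goes into the between-group comparison and looks the same as a treatment effect. Blinding the statistician protects the choices made in the analysis but leaves recorded values as they are. If the arm is also known at baseline, both ends of the change in PWV are exposed.

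**Working it through.** **1. Does the stated reason reach the measurer?**
- Section {17a} names two groups: participants, and field researchers who advise on the regimen.
- The Control group section gives the consultations to the study's nutritionist. The Intervention group section says researchers help a man choose his eating window. Section {19} gives data collection to the primary investigator.
- No sentence makes measuring PWV part of advising. The reason therefore does not cover the measuring role, while section {17b} leaves that role unblinded.

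**2. How much of PWV is open to the operator?**
- PWV = distance / transit time. At a fixed transit time, a distance taped 1% short gives a PWV 1% lower.
- Palpation, tonometer and cuff placement, and the taped distances are manual. Transit time is reported by the device, and acquisition continues until the waveforms show green. Only part of the outcome is exposed.

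**3. Baseline.** The bias in a change score is the bias at follow-up minus the bias at baseline. If the arm is unknown at baseline, knowledge of it cannot influence that term. Table 1's columns run Enrollment, Allocation, Day 1, week 3, week 6. As scheduled, baseline PWV comes after allocation.

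**4. The plan's own sample size.** From Sample size {14}: alpha 5% (two-sided, from the formula), power 80%, effect size f = 0.63.
- n = (1.960 + 0.842)² / 0.63² = 7.849 / 0.3969 = 19.78, rounded up to 20 per group. This reproduces the stated 20.
- With equal SDs this corresponds to a standardised difference of 0.63 × √2 = 0.891.

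**5. What an assumed shift would do.** The documents give no size for a measurement bias, so these shifts are assumptions. Let b be the differential shift in SDs of the PWV change, with no true effect, tested by a two-sided 5% t-test. The rejection probability comes from the noncentral t distribution with noncentrality b × √(n/2) and 2n − 2 degrees of freedom. For n = 20 and b = 0.2, the noncentrality is 0.2 × √10 = 0.632 with 38 degrees of freedom.

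| Assumed shift b | b / 0.891 | False positives, 20 per group | False positives, 24 per group |
|---|---|---|---|
| 0 | 0% | 5% | 5% |
| 0.1 SD | 11% | 6.1% | 6.3% |
| 0.2 SD | 22% | 9.5% | 10.4% |
| 0.3 SD | 34% | 15.2% | about 17% |

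The last column applies if all 24 enrolled per group are analysed, as the intention-to-treat plan with imputation intends.

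**The case against.** The strongest defence is that much of the measurement is controlled. Posture, rest and fasting are standardised, the device reports transit time, and the green-waveform criterion limits discretion over which recording is accepted. A single collector was chosen for accuracy, and handing PWV to someone else could add between-operator variation. The general practitioner and nurse are there for participants' well-being, with no tonometry role stated. All of this stands. It limits the likely bias and shapes the remedy, but it does not supply a reason for the measurer to know the arm.

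Two stronger readings are tempting and are not supported:
- A reader might infer that the primary investigator belongs to the team giving dietary advice. No section says so: the consultations belong to the nutritionist, and the researchers who help choose the window are not identified. If the investigator did advise, the reason in {17a} would reach that person. The issue would then be the combining of two roles, which nothing in the protocol requires.
- A reader might take it as established that every baseline PWV is measured with the arm known. That rests on Table 1's columns alone. Informed consent is ticked in the same column as allocation, so the columns may be broad stages. Figure 1 is not available, someone outside the research team does the allocating, and no sentence says when the measurer learns the arm. The schedule permits a baseline with the arm known but does not prove it.

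The 0.1 to 0.3 SD shifts are likewise not estimates, and nothing in the protocol shows how large a shift is plausible.

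**Conclusion.** The point holds in this form. The primary outcome is partly operator-dependent and is collected by an unblinded investigator. The only reason offered for not blinding does not cover the measuring role. The schedule as printed also puts allocation ahead of baseline PWV. This is an avoidable risk of bias in the primary comparison and should be corrected. It is not a fatal flaw, and it does not change the sample size.

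Its size is unknown. Under the assumed shifts with 20 per group, the false-positive rate would move from 5% to between about 6% and 15%. Those figures rest on no true effect, a two-sided t-test on the change in PWV, and a shift that differs between the arms.

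**What to change.** 1. For participants not yet randomised, amend Table 1 so that the envelope is opened only after the day-1 clinic measurements are recorded (PWV, anthropometry, blood tests, calorimetry, questionnaires) and before the nutrition consultation. The food diary and pedometer run through week 1 and stay after allocation. If this is already the practice, Table 1 should be corrected to show it. The order within day 1 changes; no staff or participants are added.

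2. Where existing visit staff allow, have PWV at weeks 3 and 6 acquired before the consultation by one trained operator who gives no dietary advice and is not told the arm. Ask participants not to disclose their arm. Amend sections {17a}, {17b} and {19} together, since the statements that only the statistician is blinded and that one investigator collects everything would no longer be true.

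Costs: device training for that operator, possible between-operator variation relative to measurements already taken, and some men revealing their arm. Trial status says recruitment began in October 2023, and the section on protocol amendments requires ethics approval before a change takes effect. Participants enrolled before and after the change would be measured under different procedures, so its date should be reported with the results.

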### Procedure for unblinding if needed {17b}

Considering that only the statistician will be blinded, unblinding would not be needed in any circumstances.

## Data collection and management

### Plans for assessment and collection of outcomes {18a}

Measurements will be conducted at baseline, week 3, and at the end of the intervention (week 6). All assessments will be conducted in the morning, following at least a 10-h fasting period. Before the visits, participants will be informed of the conditions required for the assessments and asked to comply with them.

#### Arterial compliance (at baseline, weeks 3 and 6)

The participants’ height will first be measured. The measurement will be taken in the morning following at least 6 h of fasting and abstinence from tobacco, alcohol, and caffeine consumption. The measurement will be taken in the supine position with their hands next to the body, following a 5-min rest at room temperature in a silent place [22].

The pulse wave analysis (PWA) will first be recorded, using a Sphygmocor (SphygmoCor Cardiovascular Management System software version 1.3; AtCor Medical Pty. Ltd., Sydney Australia) to assess the participant’s brachial systolic pressure, diastolic pressure, and pulse pressure. Three measurements will be taken and the average will be reported. Following this, aortic parameters including aortic systolic pressure, aortic diastolic pressure, aortic pulse pressure, mean arterial pressure (MAP), and heart rate (HR) will also be reported. Aortic augmented pressure, augmentation index (AIx), and AIx normalized for a heart rate of 75 beats/minute (AIx 75) will be calculated [22].

To measure pulse wave velocity (PWV), a femoral cuff will be fastened around the thigh, as high as possible. Three distances will be determined including the length from the femoral pulse sensation site to the top edge of the femoral cuff, the interval between the sternal notch to the femoral cuff, and the distance from the carotid pulse to the sternal notch in millimeters using a tape measure. The carotid pulse will be palpated and the tonometer will be positioned on it. When a regular carotid pulse is detected, the femoral cuff will be inflated. The detection of carotid waveforms will be continued until green waveforms are yielded. Then, the femoral cuff will deflate and the results will be recorded. The report will include heart rate, pulse wave velocity, and pulse transit time. Pulse transit time is the time taken for the pulse to travel from the carotid artery to the femoral artery, in milliseconds. PWV will be calculated by dividing the distance between the two arteries by the pulse transit time [22].

#### Anthropometric parameters (at baseline, weeks 3 and 6)

Weight will be measured in light clothing using electronic scales and height will be measured using a stadiometer. BMI will be calculated. Waist circumference will be measured at the midpoint between the lowest rib and the iliac crest. Bioelectrical impedance analysis (BIA; InBody 770; Smitech Pte Ltd; USA) will be undertaken to assess fat mass, muscle mass, and percent body fat.

#### Indirect calorimetry (at baseline and week 6)

To estimate energy requirements, the participant’s metabolic rate will be assessed during the fasting state (at least 6 h), using indirect calorimetry (IC). To initiate IC, the device (MetaLyzer 3B-R3 device; CORTEX Biophysik GmbH, Germany) will be calibrated. The participant will be asked to lie in the supine position and stay calm, immobile, and awake. The room will be quiet, at room temperature, and the participants should rest for at least 20 min. In case of any physical or psychological stress, the measurement will be postponed. In order to carry out IC, air samples (O2 and CO2) will be collected using a mask for a period of 20 min. Resting metabolic rate (RMR; kcal/d), diet-induced thermogenesis (DIT; kcal/d), substrate oxidation (SO; g/d), and respiratory quotient (RQ) will be measured.

#### Laboratory measurements (at baseline and week 6)

*Fasting blood tests:* An 8-ml blood sample will be collected in the fasted state to assess complete blood cell count (CBC), liver enzyme tests (aspartate aminotransferase (AST), alanine aminotransferase (ALT), and alkaline phosphatase (ALP)), high-sensitivity C-reactive protein (hs-CRP), lipid profile (triglyceride, total cholesterol, low-density lipoprotein (LDL), and high-density lipoprotein (HDL)), fasting blood glucose (FBG), and insulin concentration. Insulin resistance and β cell function will be estimated using the Homeostatic Model Assessment for Insulin Resistance (HOMA-IR) calculator [23].*Postprandial assessment:* A standard breakfast test meal containing 500 kcal (50% carbohydrates, 20% protein, and 30% fat) will be provided at the beginning and end of the study. A 5-ml blood sample will be collected at 60 min following breakfast consumption, and blood glucose and insulin levels will be evaluated. Another 8 ml blood sample will be attained and CBC, hs-CRP, blood glucose, and insulin will be assessed at 120 min following the meal consumption.

#### Laboratory measurements (at week 3)

A 5-ml sample will be collected to assess the lipid profile (triglyceride, total cholesterol, LDL, and HDL), FBG, and insulin concentration. HOMA-IR will also be evaluated.

#### Appetite status (at baseline and week 6)

Appetite status will be assessed using visual analog scale (VAS) before breakfast and one hour after the meal. This scale comprises eight questions that address appetite and desire for specific food types. The test meal palatability will also be assessed using five other questions [24].

#### Physical activity assessment (at baseline and week 6)

Physical activity level will be assessed using a pedometer (Omron ri-Axis Pedometer- Step and Activity Tracker HJ-320; Kyoto, Japan) in the first and last 7 days of the study period. The participants’ activity will also be assessed using the International Physical Activity Questionnaire (IPAQ) at the beginning and end of the study. IPAQ includes 5 domains and assesses job-related physical activity, transportation physical activity, housework, house maintenance, and caring for family, recreation, sport, and leisure-time physical activity, and time spent sitting [25, 26]. The validated Persian version of IPAQ will be used [27].

#### Sleep assessment (at baseline and week 6)

The validated Persian version of the Pittsburgh Sleep Quality Index (PSQI) [28] will be used to assess sleep duration, time of sleep, and sleep quality at baseline and week 6. PSQI comprises 7 subscales including, subjective sleep quality, sleep latency, sleep duration, habitual sleep efficiency, sleep disturbances, use of sleeping medication, and daytime dysfunction. The total score ranges from 0 to 21, and participants with scores more than 5 will be considered to have poor-quality sleep [29].

#### Cognitive function assessment (at baseline and week 6)

Cognitive function will be evaluated using the Go-No-Go (GNG) test and the Wisconsin Card Sorting Test (WCST) [30, 31]. Both tests will be conducted using PEBL (Psychology Experiment Building Language), an open-source software developed for neuropsychological function experiments [32].

GNG is a simple experimental test that assesses inhibitory neurologic function. The participants will see a square consisting of four small squares arranged in a 2 × 2 structure. A letter P (Go signal) or R (No-Go signal) is hidden under a star in each of the four small squares. A star will be randomly faded, and the participants will be asked to press the right shift button whenever they see a P letter and not to press the button when they see an R letter. Before the start of the test, a short practice will be conducted to ensure that participants understand the instructions. No Go Errors and Reaction Time for Go Responses will be analyzed to interpret the results [33].

WCST is a card-matching test that evaluates neurocognitive flexibility. The participants will be presented with four category cards which are different in terms of colors, shapes, and number of shapes. A stimulus card will be shown to the participant. He should discover the rule through trial and error and sort the cards according to the rule. When the participant sorts the cards, feedback (correct or incorrect) will be shown on the screen after each sort. After six consecutive correct responses, the rule will be changed randomly and they have to identify the new rule [34].

WCST measures the total correct score, perseverative errors score, completed categories score, and failure to maintain a set score. The number of correct matches is regarded as the total correct score. The number of categories (color, shape, or number) that are learned correctly is defined as the completed categories score. The perseverative errors score means that the participant adhered to a previously correct rule, which is not correct anymore, despite showing incorrect feedback on the screen. The failure to maintain a set score is described as the number of making errors after fully learning the present rule [34].

